### Phase 2: Training in Living Evidence tools and strategies

This phase will run concurrently with phase1, once we have completed the recruitment process of participating organizations and their members

For this project, the Epistemonikos L.OVE platform will be the tool used as part of the strategy to keep the living evidence (i.e., for generating and maintaining the living evidence process). L.OVE is a digital tool that combines a series of technological advances (including artificial intelligence algorithms) with the effort of a network of experts, to obtain and organize health evidence as soon as it is produced. A L.OVE is created for each health topic or condition (e.g., chronic obstructive pulmonary disease) and the health questions are organized by specific subtopics, such as prevention, diagnosis, therapy, or prognosis creating a comprehensive map of questions based on the PICO format (population, intervention, comparisons, and outcomes).

This platform has been chosen as the technological enabler in this project because it has several potential advantages for supporting a living evidence process that will be tested as part of the project, such as: even though it gathers information from 10 sources that are routinely examined in the Epistemonikos Database it can be programmed to search other databases relevant to the specific topic; once the PICO question is included in the L.OVE platform, the searching results are obtained very quickly (between one minute to a couple of hours); the information from saved questions is constantly updated as new evidence appears; users can create alerts when new evidence appears; the screening and selection of evidence processes can be shorter than usual thanks to artificial intelligence. The Epistemonikos -L.OVE platform has been extensively used and its effectiveness in supporting Living Evidence processes has been validated during the COVID-19 pandemic
^
29,
30
^

Therefore, this phase seeks two main objectives: 1) to train participants in the Epistemonikos tools and L.OVE platform and, 2) to evaluate the strategies used for this training.

A set of training workshops will be carried out, aimed at the members enrolled from each participating organization. Training will be focused on the processes inherent to generating living evidence based on the Epistemonikos L.OVE platform. Complimentary workshops for supporting the evaluation of certainty of updated evidence, according to the GRADE approach, will be offered depending on the degree of experience and previous training of the participants.

### Phase 3. Developing real word living evidence synthesis for KT products

This phase seeks to apply the LE-implementation framework as well as the knowledge obtained in training workshops to real-life diverse situations. According to the particular interest of the participating organizations, they can work on any of the following KT products: i) structured evidence summaries for institutional and/or public health policies; ii) health technology assessment reports, and iii) evidence-based recommendations for a CPG.

Following the principle of “learning by doing”
^
31
^, we expect members from the participating organizations to generate at least one living evidence synthesis (i.e., one PICO) needed to develop their own KT products following the LE-implementation framework (see
Figure 2 and
Figure 3). To support this task, and ensure that all the organizations' teams are receiving the same information and detailed instructions, a Manual of standardized operating procedures will make available to the participants in an online repository or as a virtual document. In this way, the participant’s skill development will be strengthened through the experience while we evaluate the LE-implementation framework performance.

**Figure 2. f2:**
[figure not shown]
Workflow for developing living evidence synthesis for priority questions of a given KT product.

**Figure 3. f3:**
[figure not shown]
Timeframe for study follow-up and data collection (key evaluations).

Each evidence synthesis will be worked on as an independent project, with an assigned working group that will involve content experts (physicians) and methodological experts from the participating organization (i.e., HTA agencies, guideline development groups, scientific organizations, research consortiums, hospital institutions) and a member of the research team (i.e., IIB Sant Pau and Epistemonikos Foundation).

### Data collection and analysis

Several measures will take place during the whole project in order to assess: the LE-implementation framework; the training workshops on Epistemonikos tools; and the capacity-building strategy used for participant health system organizations be able to implement the “living evidence” process in the development of KT products. All the participants will be invited to answer the questionnaires or the in-depth interviews to complete these assessments. The evaluations will be limited to what is necessary to meet the study objectives.
Figure 3 presents the timeframe and when evaluations will take place.

The expected size of the data collected for this assessment will be given by the number of participants who join the project from each organization.

**
*Evaluation 1. Assessment of training workshops*
**

After finishing each training session (workshop) participants will be asked to answer anonymous online surveys to assess the workshop’s materials (i.e. learning guide and objectives, support instructions and tutorials), training activities as well as the skills of the teacher who led the session and the presentation that he/she used to present the key concepts and procedures. The structured questionnaire will ask the participants to indicate his/her level of agreement (from strongly agree to strongly disagree), using a five-point Likert scale, with a series of statements that will allow us to evaluate the relevance and appropriateness of the aspects of the training workshop.

Data obtained from these surveys will be analyzed using summary measures (e.g. proportion of participants who answer each of the five Likert scale options). These data will allow researchers to redefine this part of the capacity-building strategy (if necessary). Training workshops can be also re-evaluated accordingly.

**
*Evaluation 2. Effectiveness and usability of the Epistemonikos tools and L.OVE platform*
**

All members of technical teams and task forces taking part in the study will be invited to respond to an online survey once the initial evidence synthesis process has been completed. The survey will be anonymous but will collect information about:

- Individuals' demographic characteristics and background (e.g. age, academic degree, amount of experience)

- Previous experience in developing evidence synthesis and/or systematic reviews

- Knowledge and previous experience planning and performing literature searches

- Knowledge and previous experience completing the literature screening process

This survey will evaluate the usability and performance of the Epistemonikos L.OVE platform as a tool for evidence identification, screening and maintenance of the living evidence process. The information asked to assess performance will be limited to that directly related with the tasks participants must complete by using the Epistemonikos L.OVE tools, such as planning of evidence synthesis and evidence monitoring and surveillance (including screening, classification and study selection). The information asked to assess usability will be based and limited to participants experience using the tools for the tasks mentioned above. The survey will ask participants to indicate his/her level of agreement (from strongly agree to strongly disagree), using a five-point Likert scale, with a series of statements that will allow us to evaluate the usability and performance of the tools.

Data obtained from this survey will be analyzed using summary measures (e.g. proportion of participants who answer each of the five Likert scale options).

**
*Evaluation 3. Assessment of the capacity-building strategy*
**

To achieve this objective, two complementary approaches will be used for collecting data: an online survey to all the participants and in-depth interviews to a randomly selected number of participants. The online survey will be conducted at six months after the evidence surveillance period has started. All members involved in the evidence synthesis development from participant organizations will be invited to respond to the online survey. Data to be collected in this survey will be limited to that necessary for evaluating:

Clarity, relevance and timeliness of weekly messages sent to participants informing tasks and procedures.Clarity, completeness and utility of the Manual of Standardized Operating Procedures and its instructions.Clarity and timeliness of the support given by the expert researcher assigned to the group.Clarity and timeliness of solutions provided to doubts and difficulties that arises during the process.Satisfaction with results obtained (as individual and as member of the organization group) by developing the living evidence synthesis under the learning by doing methodology.

At the end of follow-up (i.e. the end of the PICO question evidence monitoring) we will perform semi structured in-depth interviews to a randomly selected sample of participants. The randomization will be performed as a stratified random sample (including two groups/strata: a) technical team and/or taskforce members and b) team leaders), to guarantee that members from each group will be represented in the sample. This will be performed using Excel (version 16.34) software. These interviews seek to obtain information about participants´ perception of:

-The capacity-building strategy (i.e., training workshops, instructions and tutorials, accompaniment in “learning by doing” process, among other activities completed to refine the strategy within the study progress).-The LE-implementation framework and its effectiveness to guide the incorporation of living evidence synthesis processes into their usual working tasks (either for producing KT products or other evidence synthesis process to inform decision makers).

The interviews will be carried out by a third-party expert in this type of interview, with a script of questions generated by the research group. The data obtained from these interviews will be included anonymously in the Nvivo® (version 12)
^
32
^ program by the same third party and analyzed as qualitative data by an expert in the subject.

**
*Evaluation 4. Assessment of the LE-implementation Framework*
**

As presented before, the in-depth interviews will serve to evaluate the LE-implementation framework and its effectiveness in guiding the incorporation of living evidence synthesis processes into the participant’s usual working tasks in a sample of participants. To obtain information from all the participants, an online survey using Google Docs will be conducted prior to these interviews. Two types of questionnaires will be developed for this end, one for organizations technical team members and the other for organization’s group leader.

*-Technical teams' questionnaire:* This questionnaire will have a set of questions assessing participants experience with the use of the LE-implementation framework for planning and guide the living evidence synthesis.

*- Group leaders’ questionnaire:* This questionnaire will address the comprehension of the framework and its “usability” as a tool for incorporating living evidence synthesis in the current process of the organization. We will include a set of questions that permit the evaluation of how developers are taking into account the information and guidelines presented in the LE-implementation framework and/or following the pathway for guiding the inclusion of the new evidence in the already existing KT products.

Both questionnaires will be structured, asking participants to select answer options and/or to indicate his/her level of agreement (from strongly agree to strongly disagree), using a five-point Likert scale, with a series of statements that will allow us to evaluate the above-described aspects of the framework and capacity-building strategy.

Data obtained from these surveys will be analyzed descriptively using summary measures (e.g. proportion of participants answering each item option in categorical variables and median or mean with interquartile range or standard deviation for continues variables).

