### Live Evidence model

Over the last six years, members of the Cochrane Collaboration and a number of its international partners have developed the foundations of the Living Evidence model for evidence synthesis and dissemination of systematic reviews [SRs]. Living reviews are SRs that are continually updated as new evidence appears
^
9
^. The production of living reviews begins once the SR has been developed under its traditionally known quality standards (baseline review), which guarantee that the methodological approach has been the most appropriate and has ensured control of biases. Currently, the methodological approach, as well as the model for the production of living SRs are described in a series of articles
^
9–
12
^ and have been tested and adopted by some review groups within and outside Cochrane.

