## Objectives

As a research project, our main objective is to develop a capacity-building strategy to obtain, improve, and retain skills and knowledge needed to develop and use “Living evidence synthesis” among members of health system organizations in charge of developing KT products to inform health decisions.

Specific objectives are:

- To design and evaluate a framework for the incorporation of living evidence synthesis in the development of three types of KT products to inform health decisions: recommendations in clinical practice guidelines [CPG], health technology assessment reports [HTA], and structured evidence summaries [SES] for institutional or public policies.

- To build capacity among members of health system organizations in the use of innovative and effective tools to support the generation and maintenance of living evidence synthesis.

- To develop living evidence synthesis for KT products to inform health decisions in a real setting

- To assess the effectiveness and usability of the Epistemonikos-L.OVE platform as a tool for keeping the living evidence process, as part of the development and updating of the different KT products

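### The only specified L.OVE survey is triggered when the initial synthesis is completed, so its maintenance, alert and updating items may be answered with little or no experience of those tasks

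*Protocol article*

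**What the plan says.** The last specific objective under Objectives is "To assess the effectiveness and usability of the Epistemonikos-L.OVE platform as a tool for keeping the living evidence process", in developing and updating the KT products. The instrument for it is Evaluation 2, under Data collection and analysis:

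- **Timing.** Members of the technical teams and task forces "will be invited to respond to an online survey once the initial evidence synthesis process has been completed". No second L.OVE survey is described.
- **Scope.** L.OVE is assessed "as a tool for evidence identification, screening and maintenance of the living evidence process".
- **Performance items.** These concern tasks done with the tool, "such as planning of evidence synthesis and evidence monitoring and surveillance (including screening, classification and study selection").
- **Usability items.** These "will be based and limited to participants experience using the tools for the tasks mentioned above".

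Evaluation 3, in the same section, fixes its timing differently: "The online survey will be conducted at six months after the evidence surveillance period has started". Interviews with a random sample follow when evidence monitoring ends, and the Evaluation 4 questionnaires go out before those interviews.

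**The concern.** Evaluation 2 sets a sensible standard for its usability items: they rest on what respondents have themselves done with the tool. Its trigger, however, is the end of the initial synthesis. Upkeep, alerts and incorporation of new evidence are mainly done after that. If surveillance has hardly begun when the survey arrives, answers on those tasks reflect expectation, or a midpoint chosen for want of experience. They would still be tabulated as proportions on a five-point scale, and the text states no way to tell a neutral rating from no exposure.

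The stake is the part of the fourth objective that concerns keeping evidence living. The Phase 2 section names constant updating of saved questions and alerts for new evidence among the advantages that the project will test. How well these work in practice is best judged after some time in surveillance.

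**Working it through.** The article gives no sample size, power or error rate that bears on this point, and the survey analysis is descriptive. The check is therefore one of order and coverage, followed by a small illustration.

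**1. Order of events.**
- Evaluation 2 is triggered by completion of the initial synthesis.
- Evaluation 3 speaks of surveillance as a period that starts, and counts six months from that start.
- The Brainstorming meetings section lists planning, surveillance and monitoring, and integration of new evidence as separate times in the process.
- The introductory section on the Live Evidence model says: "The production of living reviews begins once the SR has been developed under its traditionally known quality standards (baseline review"). This is background on living reviews in general. It supports the order but does not set this project's schedule.

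The order that best fits the text is: initial synthesis, L.OVE survey, surveillance, six-month survey, Evaluation 4 questionnaires, interviews. This is an inference. Figure 3, which gives the evaluation timeframe, is not shown, and no visible sentence dates the start of surveillance.

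**2. Which items are affected.**

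| Task rated in Evaluation 2 | Part of the initial synthesis? | Timing |
|---|---|---|
| Planning | Yes | Valid |
| Identification, screening, classification, selection | Yes | Valid |
| Maintenance, alerts, updating | Mainly afterwards | In doubt |

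The protocol places screening, classification and selection under the monitoring heading, so only part of that heading is in doubt.

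**3. Whether a later instrument covers the gap.**

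| Instrument | Listed content | L.OVE named? |
|---|---|---|
| Six-month survey (Evaluation 3) | Weekly messages, manual, support, solutions to difficulties, satisfaction | No |
| End-of-monitoring interviews (sample only) | Capacity-building strategy, framework | No |
| Evaluation 4 questionnaires | Framework and capacity-building strategy | No |

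The Design section says that information on using the tools to keep evidence living is gathered throughout phases 2 and 3. No L.OVE measurement after Evaluation 2 is specified to carry that out.

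**4. What non-performers could do to a reported proportion (illustration).** The Sampling section seeks at least two organizations of each of three types and asks each for at least three members. That floor is 3 × 2 × 3 = 18 people. Assume that all 18 answer, that k of them have not performed the task and choose the midpoint, and that everyone who has performed it agrees. The reported share agreeing is then (18 − k)/18, while the share among performers is 100%.

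- k = 0: 18/18 = 100%
- k = 3: 15/18 = 83.3%
- k = 6: 12/18 = 66.7%
- k = 9: 9/18 = 50.0%

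The values of k are assumptions, as the article gives no basis for choosing one. If non-performers instead answer from favourable expectation, the error runs the other way. Neither its direction nor its size is known in advance.

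**The case against.** The strongest reply is that the order of events is not established. Figure 3 would settle it. The Extended data also list an execution plan and an operations manual, neither of which is shown. The Phase 2 section says that a question saved in L.OVE is updated constantly and that users can set alerts, so some updating could run during the initial synthesis. Completion of that synthesis is also an earliest time, not a deadline, and late respondents may have had some surveillance experience. This stands, and it limits confidence to moderate. It does not remove the point, because no minimum exposure is required.

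A second reply is that the limit to experience, "will be based and limited to participants experience using the tools for the tasks mentioned above", is already a safeguard. It is a partial one. It restricts the usability questions, but the text does not say how someone without that experience should answer or be counted.

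A third reply is that later data may fill the gap, through the Design section's statement or through interviews about a strategy of which L.OVE is part. The interviews might touch on the platform. They reach only a sample, and their listed topics do not name it.

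A reader might go further and infer that every respondent will have about zero months of surveillance exposure, and that the fourth objective therefore fails. The documents do not support that. They give no such figure, much of the monitoring heading is exercised in the initial synthesis, and the questionnaire itself is not shown.

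**Conclusion.** The point holds in a limited form. The only specified L.OVE survey is tied to the end of the initial synthesis, it asks for no minimum surveillance exposure, and no later instrument shown names the platform. Its maintenance, alert and updating items may therefore be answered with little or no experience of those tasks. This weakens one part of one of the four specific objectives: whether L.OVE works for "as a tool for keeping the living evidence process, as part of the development and updating of the different KT products". The planning, identification, screening and selection results are unaffected.

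This rests on two assumptions: that surveillance begins at or near the end of the initial synthesis, and that Figure 3 shows no later L.OVE survey. If Figure 3 shows substantial overlap or a repeat survey, the point falls away or shrinks to the missing response option. Should-fix, moderate confidence.

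**What to change.** 1. Keep Evaluation 2 at completion of the initial synthesis, for the planning, identification, screening and selection items.
2. Move the maintenance, alert and updating items to the six-month survey, or repeat them there. That survey already goes to all members involved in developing the syntheses. Its list of content in Evaluation 3 is worded as a limit, so L.OVE must be added to it.
3. Add a response option for not having performed the task. Report those proportions among respondents who performed it, with their number shown.

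The cost is a slightly longer six-month survey, with no extra contact. If the items are repeated, the two rounds can be compared only in aggregate, because Evaluation 2 is anonymous. At the stage given under Study status, training was complete and the draft framework was awaiting expert assessment, so the change looked feasible. Once monitoring has ended, the same information could be had only by recall.

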### Dissemination

The dissemination of this project’s results seeks to achieve four objectives: 1) make the successful strategies used for building capacity in the production of LE synthesis as part of KT products, known among the community of methodologists working on synthesis of evidence to inform health decisions; 2) make the final results of the “living evidence synthesis” known to physicians and clinical experts in each area of interest; 3) promote the use of structured summaries of evidence among physicians and policy makers (from healthcare institutions and public sector); 4) promote the use of technological enablers such as the L.OVE platform and Epistemonikos tools for supporting evidence synthesis tasks among the HTA and CPG developers.

**
*Specific actions.*
** The results related to the capacity-building strategy will be presented in the KT thematic sessions of the Cochrane Colloquium and G-I-N Conference. To reach a broader community we will contact organizers of KT events of specific interest (i.e. the Oxford Health Policy Forum; the Evidence Live Oxford and the Canadian Health System Forum) with the aim of getting a slot for presenting our results.

A paper presenting the capacity-building strategy “Living Evidence to inform health decisions” and its assessment results will be published in an international journal.

The final overviews (evidence synthesis) and evidence summaries produced by participant organizations will be published on the organizations’ websites.

A special meeting with the HTA agencies’ staff will be planned to present the results as well as protocols and procedures for developing living overviews, using Epistemonikos tools and platforms to inform decision-makers. To reach a broader public, the project results will be presented in the annual HTAi meeting.

The updated CPGs will be published for use by the scientific community according to the policy of each organization.

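### L.OVE's effectiveness is an objective and its advantages are to be tested, but the only stated L.OVE outcome is users' Likert agreement, which supports perceived usability and performance only

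*Protocol article*

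**What the plan says.** The protocol article makes the commitment in three places. The last of the four specific objectives (Objectives) reads: "To assess the effectiveness and usability of the Epistemonikos-L.OVE platform as a tool for keeping the living evidence process". The section on Phase 2 gives as the reason for choosing the platform that "it has several potential advantages for supporting a living evidence process that will be tested as part of the project". It then lists the advantages, including search results within one minute to a couple of hours, and that "the screening and selection of evidence processes can be shorter than usual thanks to artificial intelligence". The heading of Evaluation 2 (Data collection and analysis) again names effectiveness.

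The body of Evaluation 2 is narrower: "This survey will evaluate the usability and performance of the Epistemonikos L.OVE platform as a tool for evidence identification, screening and maintenance". The instrument is one anonymous online survey after the initial evidence synthesis. It has background questions and a set of statements: "The survey will ask participants to indicate his/her level of agreement (from strongly agree to strongly disagree), using a five-point Likert scale". The analysis is the proportion of participants choosing each option.

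On the setting: the section on the Epistemonikos project says that Epistemonikos developed L.OVE. The Phase 3 section names the Epistemonikos Foundation, with IIB Sant Pau, as part of the research team that supplies a member to each working group. One of the four dissemination objectives is to "promote the use of technological enablers such as the L.OVE platform and Epistemonikos tools".

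**The concern.** Effectiveness of a search and surveillance tool is a matter of what it retrieves, how soon and at what workload. Agreement with statements records how users felt about it. A platform can be pleasant to use and score well while returning an incomplete set of studies, and the survey alone would not separate the two cases.

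If the plan is followed as written, objective 4 will be answered, and effectiveness reported, from perception data alone. Readers in health technology assessment and guideline groups could take that report as evidence that the platform finds the right studies faster than their present process. The project would hold no stated data on that question.

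**Working it through.** No arithmetic is needed. The article gives no sample size, threshold or error rate for this evaluation, so there is no figure to reproduce. The check is to follow each promise to the data meant to support it.

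Step 1: the advantages listed under Phase 2, set against what Evaluation 2 states.

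| Listed advantage | What a test would need | Stated for L.OVE |
|---|---|---|
| Draws on 10 sources and can be set to search others | Retrieval against a known set of eligible studies | Likert agreement |
| Search results in one minute to a couple of hours | Recorded search time | Likert agreement |
| Saved questions constantly updated | Delay from a study's appearance to its entry | Likert agreement |
| Alerts on new evidence | Whether and when alerts arrived | Likert agreement |
| Screening and selection shorter than usual | Recorded time, plus a time for the usual process | Likert agreement, with prior screening experience as a background question |

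An objective measure is stated for 0 of the 5. The first and fourth can fairly be read as features of the platform. The second and fifth are plainly measurable, and the fifth is comparative.

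Step 2: whether another evaluation fills the gap.

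- Evaluation 1 rates workshop materials, activities and teaching.
- The Evaluation 3 survey rates the weekly messages, the manual, the support given, the handling of difficulties, and satisfaction.
- The in-depth interviews cover perceptions of the capacity-building strategy and of the implementation framework. L.OVE is not a listed topic.
- Evaluation 4 rates the framework.

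None adds an L.OVE outcome. The Design section says that information on use of the Epistemonikos tools is collected throughout phases 2 and 3, but the only L.OVE outcome then described is the Evaluation 2 survey.

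Step 3: what the stated data can carry. Proportions per Likert option, from people who used the tool on their own question, describe perceived usability and perceived performance of the tasks they did. With no recorded retrieval, time or workload and no external comparator, they do not show effectiveness. The text of Evaluation 2 nearly says this itself: it moves from effectiveness in the heading to usability and performance in the body, and bases usability on participants' experience.

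**The case against.** The other side has real points.

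- Respondents are professionals who do evidence synthesis for a living. The survey asks about their earlier experience of searching and screening, so each has a personal idea of what is usual. This stands: there is a reference, though a subjective and unrecorded one.
- Some organisations have existing products and may notice a missing study. This also stands, so it would be too strong to say that users can never detect a miss. But no step asks them to check or to count.
- The Evaluation 2 questionnaire and the operations manual are not shown, and items on time or completeness may exist. That is possible, but the article itself fixes the response as agreement and the summary as proportions. The point is therefore about a stated choice, not an omitted detail.
- L.OVE is the last of four specific objectives, and the main aim is capacity building. This limits the weight of the point but does not remove the mismatch.
- The article describes the platform's effectiveness as already validated during the COVID-19 pandemic. If that is relied on, this project need not claim to assess it.

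Two stronger readings are tempting. A reader might infer that the developer's presence in the team biases the answer. The article supports only that the developer is on the team. It also describes Epistemonikos as non-profit and free to use, names IIB Sant Pau as the lead group, keeps the survey anonymous and asks participants to declare conflicts of interest. No financial interest is established. A reader might also infer that the platform will be promoted whatever the survey shows. The dissemination aim carries no condition on the findings, but it does not say that either.

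**Conclusion.** The point holds as a mismatch between claim and measure. Effectiveness is promised in objective 4 and in the Evaluation 2 heading, and a test of the listed advantages is promised under Phase 2. The stated data can answer only for perceived usability and perceived performance. The size is qualitative: one of four specific objectives is affected, and the capacity-building and framework evaluations are untouched. A larger survey would not help, since more respondents would sharpen an estimate of opinion and still say nothing about retrieval or time.

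The conclusion assumes that the article's description of Evaluation 2 is complete as to the type of data collected. If an unseen document already provides for logged time or a retrieval check, the article should say so and the point falls away to that extent.

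**What to change.** Main change, wording only:

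1. In objective 4 and in Evaluation 2, replace 'effectiveness and usability' by 'perceived usability and performance'.
2. Under Phase 2, remove the statement that the advantages will be tested, or limit it to users' perception of them.
3. Make the fourth dissemination objective depend on the findings.

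This costs an edit and no data.

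If an effectiveness claim is to be kept, add a short log per PICO question with search hours, screening hours and records screened per included study, and report it descriptively. Hours alone will not show that screening is shorter than usual; that comparison also needs a recorded time for a comparable usual process. Report relative recall (included studies that L.OVE retrieved, divided by all included studies in the reference set) only where the reference set was found independently of L.OVE, such as a pre-existing product. A baseline built with L.OVE would be circular, because its studies would be recalled by construction. Where no independent set exists, report time and workload only.

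The cost is a new log sheet, since the article describes no time records, and some abstraction work per question. At the enrolment target of 3 organisation types × 2 organisations, with at least one synthesis each, that is at least 3 × 2 × 1 = 6 questions. On the study status given, training is complete and the framework draft still awaits expert assessment, so the log could probably start with the Phase 3 work.
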